
### Study procedures

Clinical assessment will be performed preoperatively (baseline), during surgery, at day three, at day ten, eight weeks, five months and one year after surgery. A link to all (online) questionnaires will be sent to the patients at baseline and one year after surgery. In addition, a link of the qDASH, OES, VAS and MEPS will be sent eight weeks and five months after surgery. An independent and blinded researcher will perform postoperative assessment (Fig. 1).

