### Sample size calculation

The primary study question addresses improvement in active elbow flexion-extension arc and pronation-supination arc at one year. A power analysis indicated that a total sample size of 72 patients (24 patients in each cohort) would provide 80% power (b = 0.20, a = 0.05) to detect a clinically relevant difference of ten degrees in improved flexion arc. To account for a possible loss to follow-up of 20 to 25%, we anticipate enrolling 30 patients in each cohort; 90 patients in total for this study.

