### Statistical analysis

The data will be presented in line with the SPIRIT statement. Analyses will be performed according to the intention-to-treat principle, according the following example: when a patient crossed over from the ‘CPM’ group, to the ‘PT’ group (i.e. still having supervised physical therapy, but the patient refuses CPM, or does not tolerate CPM), analysis will be according to initial randomization, with this patient in this particular example still being analyzed in the ‘CPM group’ although the patient did not receive CPM, he or she will be analyzed according the intention to treat in this cohort. After completing the trial, a post-hoc power analysis will be performed again, to address and account for alpha post-RCT with known standard deviation in our three study groups.

Patients’ baseline characteristics will be compared between the three groups. Depending on the distribution of the gathered data, Chi-square tests or Fisher’s Exact tests will be used for categorical variables, and ANOVA or Kruskal Wallis tests for continuous variables.

For our primary outcome, the improvement in active elbow flexion-extension arc in degrees after one year, an ANOVA will be performed to compare the three groups. For the other time-points and the other continuous outcome parameters (flexion, extension, flexion contracture, forearm rotation, pronation, supination, qDASH scores, OES scores, MEPS scores, SF-36 scores, CESD-R scores, VAS pain scores, PCS scores and WORQ scores and number of additional surgeries) also the changes compared to the pre-randomization scores will be compared between cohorts using ANOVAs. An alpha correction for multiple comparisons on the same secondary outcome measure will be applied.

Differences in categorical outcome parameters (MEPS) will be compared between the groups at each time-point using the Chi-square test for trend. Furthermore, the association between the arc of elbow flexion and extension and the qDASH scores will be analyzed at enrolment and at the six- and twelve-month evaluations using Spearman correlation. Also in these cases an alpha correction for multiple comparisons on the same secondary outcome measure will be applied.

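### The primary one-year ANOVA of change in flexion-extension arc omits the baseline arc as a covariate: valid under randomisation, but usually less precise than ANCOVA

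*Protocol article*

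**What the plan says.** The Statistical analysis section of the protocol article fixes the endpoint and the test together. The endpoint is introduced with the words "For our primary outcome, the improvement in active elbow flexion-extension arc in degrees after one year". The test is then stated in the same sentence, which says that "an ANOVA will be performed to compare the three groups". No baseline term or other covariate is named. For the other time-points and the other continuous outcomes, the next sentence says that "also the changes compared to the pre-randomization scores will be compared between cohorts using ANOVAs". Both the endpoint (a change) and the model (ANOVA on arm alone) are therefore fixed in the text.

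The Sample size calculation section plans 72 evaluable patients, 24 per arm, for 80% power at alpha 0.05 "to detect a clinically relevant difference of ten degrees in improved flexion arc". It gives no standard deviation and no baseline to one-year correlation. Enrolment is raised to 90 for "a possible loss to follow-up of 20 to 25" per cent. Under Study procedures, clinical assessment takes place "preoperatively (baseline), during surgery, at day three, at day ten, eight weeks, five months and one year after surgery", so the baseline arc will already be on file.

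**The concern.** A change score uses the baseline, but with a coefficient fixed at 1. The slope of the one-year arc on the baseline arc is r/q, which equals 1 only if r = q. Otherwise the change score over- or under-corrects, and part of any chance baseline difference between arms stays in the estimate.

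This matters more here than in a large trial. There are about 24 evaluable patients per arm, so chance differences in starting arc will not be small. Under Study population, patients qualify either by an arc below 100° or by a contracture of more than 30° against the other side, so starting arcs, and with them the room for gain, can differ widely. At stake is precision on a 10° target in a trial planned at 80% power with little to spare.

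**Working it through.** **Inputs from the article.** Target difference 10°; 24 evaluable per arm (72 in all); alpha 0.05; power 80%; endpoint is change in arc at one year; no covariate.

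**Inputs not in the article, so assumed.** The correlation r between baseline and one-year arc, and the SD ratio q = baseline SD / one-year SD. Both are varied below.

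**Step 1: the plan's own figure.** The 72 cannot be reproduced forwards because no SD is stated. Solving backwards for the SD of the change at 24 per arm and 80% power gives 12.1° for a two-sided t comparison of two arms. For the three-group F test it gives 10.9° with the third mean midway and 12.6° with one arm differing. With 12.1°, the standardised difference is 10/12.1 = 0.826 and the noncentrality is 0.826 × √(24/2) = 2.86. The enrolment of 90 equals 72/(1 − 0.20). At 25% loss, 90 × 0.75 = 67.5 patients would be evaluable, with about 77% power under the same SD.

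**Step 2: variance ratio.** With s the one-year SD:

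- Var(change) = s²(1 + q² − 2rq)
- Residual variance of ANCOVA = s²(1 − r²)
- Ratio, ANCOVA to change = (1 − r²)/(1 + q² − 2rq)
- Var(change) minus ANCOVA residual variance = s²(q − r)²

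The last line is never negative, so apart from one degree of freedom ANCOVA is never less efficient. It is zero exactly when r = q, where the slope really is 1.

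**Step 3: equal SDs (q = 1).** The ratio reduces to (1 + r)/2. Power is for 24 per arm, with the change-score analysis set at 80%.

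| r | Variance ratio | SE reduction, 1 − √ratio | Noncentrality, 2.86/√ratio | Power | Evaluable patients for 80% (72 × ratio) |
|---|---|---|---|---|---|
| 0.3 | 0.65 | 19% | 3.55 | about 94% | 47 |
| 0.5 | 0.75 | 13% | 3.30 | about 90% | 54 |
| 0.7 | 0.85 | 8% | 3.10 | about 86% | 62 |

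The three-group F test, with one further degree of freedom spent on the covariate, gives the same powers to within a percentage point.

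**Step 4: unequal SDs.**

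| q | r = 0.2 | r = 0.5 | r = 0.8 |
|---|---|---|---|
| 0.5 | 0.91 | 1.00 | 0.80 |
| 0.75 | 0.76 | 0.92 | 0.99 |
| 1.25 | 0.47 | 0.57 | 0.64 |

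At q = 0.75 and r = 0.7 the ratio is (1 − 0.49)/(1 + 0.5625 − 1.05) = 0.51/0.5125 = 0.995, which is practically no gain. At q = 1.25 and r = 0.5 it is 0.75/1.3125 = 0.57, a larger gain than under equal SDs.

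**Step 5: the same loss seen in a single trial.** With q = 1, a baseline difference D between two arms shifts the expected change-score difference by (1 − r) × D in size. The single-visit SD is 12.1/√(2(1 − r)), and one standard error of D is that SD × √(2/24).

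- r = 0.3: SD 10.2, standard error 2.95, shift 0.7 × 2.95 = 2.1°
- r = 0.7: SD 15.6, standard error 4.51, shift 0.3 × 4.51 = 1.4°

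A baseline imbalance of one standard error thus moves the estimate by about 1.4° to 2.1° against a 10° target. Over repeated randomisations these shifts average to zero. They are the lost precision of Step 3 in another form and do not add to it.

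**The case against.** The strongest reply is that nothing here is an error. Under randomisation the ANOVA of change is unbiased and holds its type I error. The baseline is used, not thrown away, and the choice between change score and ANCOVA is one of efficiency. The gain also depends on two quantities that the article does not give. The equal-SD figures are not the worst case: eligibility restricts the starting arc, q below 1 is possible, and at q = 0.75 with r = 0.7 there is almost nothing to gain. All of this stands and limits the point to precision of uncertain size. It does not rescue the choice, because Step 2 shows that the unadjusted analysis cannot be the more efficient one beyond a single degree of freedom.

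A reader might go further and infer that the one-year ANOVA drops the 20 to 25% of patients without a one-year visit, and so contradicts the statement that "Analyses will be performed according to the intention-to-treat principle". The article does not support that. It calls the loss possible. Under Ethical considerations, patients who miss a visit are invited back at no cost. Nowhere does it say whether patients without a one-year value are excluded or imputed, and that is commonly left to an analysis plan, which is not shown. Its intention-to-treat statement is explained only by a cross-over example, with which the ANOVA agrees.

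A reader might also infer bias from selective dropout. If loss depended on recovery in the same way in every arm and there were no true effect, the arms would be selected alike and the expected difference would stay at zero. A material bias under no effect needs dropout that works differently by arm, and nothing in the article suggests that.

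**Conclusion.** The point holds as one of efficiency. The article fixes an unadjusted ANOVA of change for the primary outcome and extends it to the other continuous outcomes, where a baseline-adjusted analysis would be at least as precise but for one degree of freedom. If baseline and one-year SDs are equal and r lies between 0.3 and 0.7, the standard error falls by 19% to 8% and 80% power becomes about 94% to 86%. If r is close to q the gain is near zero; if the baseline SD exceeds the one-year SD it is larger. Both r and q are assumptions. It is neither a claim of bias nor a finding about missing data or intention to treat.

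**What to change.** Replace the primary ANOVA of change by an ANCOVA of the one-year flexion-extension arc on arm, with the baseline arc as a continuous covariate. Taking the change as the response in the same model gives identical arm differences, so the endpoint can still be reported as improvement. Use the same adjustment, each with its own baseline score, for the other time-points and continuous outcomes that have a baseline. The number of additional surgeries, which the article lists among these outcomes, has no natural baseline score and would stay outside this rule.

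The cost is one degree of freedom per model and a change of wording in the analysis plan, made before outcome data are seen. No new visit, measurement or patient is needed. A mixed model that also uses the eight-week and five-month arcs is an optional extension. It spends more parameters, and the point made here does not depend on it.

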**Methods/design:**

The SET-Study (Stiff Elbow Trial) is a single-centre, prospective, randomized controlled trial. The primary objective of this study is to compare the active Range of Motion (ROM) (flexion arc and rotational arc) twelve months after surgery between three groups. The first group will receive in-hospital CPM in combination with early motion Physical Therapy (PT) supervised by a physical therapist, the second group will receive only in-hospital early motion PT supervised by a physical therapist and the third group will receive outpatient supervised PT from postoperative day seven till ten. Secondary outcome measures will be Patient Reported Outcome Measures (PROMs) including the Mayo Elbow Performance Score (MEPS), the Oxford Elbow Score (OES), the quick Disabilities of Arm, Shoulder and Hand (qDASH) score, Visual Analogue pain Scale in rest and activity (VAS), Pain Catastrophizing Scale (PCS), the Short Form (SF)-36, the Centre for Epidemiological Studies Depression Scale Revised (CESD-R) and the Work Rehabilitation Questionnaire (WORQ) for the upper limb.

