## Methods

### Study design

The SET-study is a three-arm, prospective, single-centre, randomized controlled trial with twelve months of follow-up. One teaching hospital in the Netherlands will participate. Patient will be included in one of the three post-surgical release rehabilitation arms after index surgery for stiff elbow:In-hospital Continuous Passive Motion with Early Motion Supervised Physical Therapy (CPM)In-hospital Early Motion Supervised Physical Therapy (PT)Outpatient Supervised Physical Therapy from postoperative day 7–10 (DPT)

In our hospital, the gold standard as rehabilitation protocol after capsule release of the stiff elbow includes CPM with physical therapy. Therefore, the control-group of our study is group one (CPM-group).

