Secondary outcome measures are PROMs which consist of;The Oxford Elbow Score (OES) [17, 18], which reflects both function and pain following elbow surgery. The OES consists of three domains; pain, function and social-psychological. Each domain comprises of 4 questions with 5 response options per question. Each response is scored 0 to 4, with 0 representing greater severity. Scores for each domain are calculated as the sum of each individual item score within that domain. These scores are then converted to a metric score between 0 and 100 (a lower score represents greater severity). The Minimal Clinically Important Difference (MCID) for the OES is 10 points [19].The Mayo Elbow Performance Score (MEPS) [20], which is based on 4 domains (pain, range of motion, stability and elbow function). A total score between 90 and the maximum 100 points is considered excellent; 75–89 is good; 60–75 is fair and less than 60 points is poor. The MCID for the MEPS is 15 points [21].The quick Disabilities of Arm, Shoulder and Hand (qDASH) score [22–24], which is scored in two components: the disability/symptom section (11 items, scored 1–5) and the optional high-performance sport/music or work modules (four items, scored 1–5). The quick-DASH is designed to measure physical function and symptoms in patients with any or several musculoskeletal disorders of the upper limb. The MCID for the qDASH is 10 points [25].The Visual Analogue pain Scale in rest and activity (VAS) [26], which is a one-dimensional measure of pain intensity scored between 0 and 100. 0 is no pain and 100 is the maximum of pain. The MCID for the VAS 0–100 is 14 points [27].The Pain Catastrophizing Scale (PCS) [28], which consists of 13 items reflecting catastrophic thinking in relation to pain. The PCS total scores ranges from 0 to 52, in which a higher score is related to an experienced higher level of physical and emotional distress associated with the pain condition. The MCID for the PSC is not established.The Short Form (SF)-36 [29], which measures the quality of life. The SF-36 consists of eight scaled scores, which are the weighted sums of the questions in their section. Each scale is directly transformed into a 0–100 scale on the assumption that each question carries equal weight. The lower the score the more disability. The MCID for the SF-36 is not established.Centre for Epidemiological Studies Depression Scale Revised (CESD-R) [30], which consists of 20 items, is a screening test for depression and depressive disorder. Patients are asked to fill in how many times they were experiencing specific symptoms (not at all or less than one day = 0, 1–2 days = 1, 3–4 days = 2, 5–7 days = 3, nearly every day for 2 weeks). The sum of the answers in combination with DSM criteria is representative for the severity of the depression. The MCID for the CESD-R is not established.The Work Rehabilitation Questionnaire (WORQ) for the upper limb is a questionnaire specific for work-related limitations in patients with upper extremity musculoskeletal disorders. The content includes four categories: exertion, dexterity, handling tools & equipment, and mobility. Patients are asked to fill in how difficult it was to perform several activities while performing their job (caused by symptoms of the affected upper extremity). Patients have to rate their difficulty on a 6-point scale: 0 = not applicable (in my job), 1 = not at all, 2 = slightly, 3 = moderately, 4 = very, 5 = extremely, or I cannot do this. The MCID for the WORQ is not established.

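### The MEPS categories get a trend test across three arms with no declared order, so the result depends on how the arms are numbered; the MEPS bands also overlap at 75

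*Protocol article*

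**What the plan says.** The Statistical analysis section of the protocol article plans two between-arm analyses of MEPS.

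- MEPS scores are listed among the continuous outcomes whose change from baseline is compared between the three cohorts by ANOVA.
- MEPS classes have a separate analysis: "Differences in categorical outcome parameters (MEPS) will be compared between the groups at each time-point using the Chi-square test for trend".

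The classes are defined under Outcome measures. Excellent runs from 90 to 100, and then "75–89 is good; 60–75 is fair and less than 60 points is poor". The same section describes MEPS as a score "which is based on 4 domains (pain, range of motion, stability and elbow function").

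On the arms, Study design states: "The SET-study is a three-arm, prospective, single-centre, randomized controlled trial with twelve months of follow-up". It lists CPM, PT and DPT and names CPM as the control. Neither there nor elsewhere does the article give the arms an order or scores.

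On collection, the abstract counts MEPS among the patient-reported measures. Study procedures says "A link to all (online) questionnaires will be sent to the patients at baseline and one year after surgery" and adds that "a link of the qDASH, OES, VAS and MEPS will be sent eight weeks and five months after surgery". It also says: "An independent and blinded researcher will perform postoperative assessment".

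**The concern.** A chi-square test for trend on a three-arm by four-class table asks whether the outcome rises or falls steadily along a numbered sequence of arms. The stated aim is to find differences among three rehabilitation protocols, and the Ethical considerations section says the literature favours none of them. A test that presumes a direction along an undeclared sequence does not match that aim, nor the ANOVA planned for the same instrument in the same section.

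Two things are at stake. The numbering of the arms can decide whether the categorical result is significant, and the article does not fix it. And if the middle-coded arm differs from two similar outer arms, this analysis will report nothing.

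A smaller defect sits in the class definitions: a patient scoring 75 meets two of them, so the table cannot be filled without a further decision.

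**Working it through.** **Inputs.** Three arms, 24 evaluable patients each, N = 72 (Sample size calculation). Alpha 0.05. Four ordered MEPS classes (Outcome measures). The article gives no expected class shares, so those below are assumptions, in the order poor/fair/good/excellent:

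- Set A: lower arm 15/25/35/25%, better arm 3/10/30/57%, midway arm 9/17.5/32.5/41% (the average of the two).
- Set B: lower arm 25/35/25/15%, middle arm 15/28/32/25%, better arm 7/20/33/40%.

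The article has no figure of its own on this point to reproduce.

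**Step 1: what the trend test sees.** The statistic is M² = (N − 1)r², on 1 df, where r is the correlation between arm score x and class score y. With equal arms of size n and scores 1, 2, 3, the numerator of r is Σ(x − 2)y = n × (mean of third arm − mean of first arm). The middle arm drops out of it. This is structural and does not depend on the assumed shares.

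**Step 2: a worked table.** Take counts of 6/8/6/4 in CPM, 2/5/8/9 in PT and 6/8/6/4 in DPT, with classes scored 0 to 3.

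- Arm totals are 32, 48 and 32, which sum to 112.
- The class counts are 14/21/20/17, so Σy² = 21 + 80 + 153 = 254.
- Syy = 254 − 112²/72 = 79.78, and Sxx = 24 × (1 + 0 + 1) = 48.
- Coded CPM-PT-DPT: Sxy = −32 + 0 + 32 = 0, so M² = 0 and p = 1.00.
- Coded CPM-DPT-PT: Sxy = −32 + 0 + 48 = 16, so r² = 256/(48 × 79.78) = 0.0669, M² = 71 × 0.0669 = 4.75 and p = 0.029.
- Kruskal-Wallis, which needs no coding: H = 6.36 on 2 df, p = 0.042.

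The same data give p = 1.00 or p = 0.029 according to the numbering.

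**Step 3: power by simulation**, 24 per arm, trend test coded CPM-PT-DPT. Ranges show variation between repeated simulations.

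| Scenario | Shares | Trend | Kruskal-Wallis |
|---|---|---|---|
| No difference | A and B | 4–5% | 4–5% |
| Only PT better | A | 5% | 77–78% |
| Only PT better | B | 4% | 77% |
| Only DPT better | A | 71–73% | 77–78% |
| Only CPM better | A | 72% | 77–78% |
| CPM worse than the other two | B | 75% | 76% |
| Steady gradient | A | 74% | 63–65% |
| Steady gradient | B | 74% | 63% |

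In the PT-only scenario under Set B, renumbering so that PT is not in the middle lifts the trend test from 4% to 73–74%. In the PT-only scenario under Set A, a one-way ANOVA run on the four coarse classes has 77% power.

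**Step 4: the bands.** Checking every integer from 0 to 100 against the four bands, 75 is the only score that falls in two, and no score falls in none.

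**Step 5: collection.** MEPS is sent by link, and two of its four domains are range of motion and stability. Outcome measures describes goniometry for motion. No section describes a stability examination, and none says who scores either domain.

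**The case against.** The best defence is that the arms can be ranked. The Intervention section runs from CPM plus early therapy, through early therapy alone, to therapy starting at day 7–10, which is a sequence in amount and earliness of motion. The Background offers a biological argument along the same axis. On that reading a trend test is legitimate, and it has more power if the gradient is real (74% against 63–65%). The scores could also sit in a SAP that is not shown. This stands in part: the trend test is not invalid in itself, and a declared order would remove the arbitrariness of the numbering. But the article draws no ordering from that rationale, treats the arms as unordered in the neighbouring ANOVAs, and would still have a test blind to the middle arm.

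A second defence is that little hangs on this analysis. That stands. A reader might infer that the trial could miss a PT-only benefit on MEPS altogether; the article does not support this, because MEPS scores are also compared by a 2-df ANOVA that does not depend on arm numbering.

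A reader might also infer that patients who know their arm rate objective domains that a blinded assessor examines at the same visits. The text does not go that far. It says a link is sent, but not who scores motion and stability. That patients know their allocation is a reasonable inference from the interventions, not a statement. No stability examination is described at all.

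**Conclusion.** The point holds for the supplementary categorical analysis of one secondary outcome. As written, its result depends on an undeclared numbering of the arms, and it has no more than chance power (4–5%) against a benefit confined to the middle-coded arm, where Kruskal-Wallis has about 77%. Those percentages rest on assumed class shares, 24 patients per arm, and coding in the order the arms are listed. The blindness itself follows from the formula.

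The primary outcome and the continuous MEPS comparison are untouched. The overlap at 75 is real but small: such a patient has two classes, not none, and one boundary change resolves it. On collection, the evidence supports only tying the motion domain to measurements already planned. It does not support changing how stability is obtained.

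**What to change.** - **Test.** Compare the ordered MEPS class between arms with a 2-df test that keeps arm nominal: Kruskal-Wallis (already named in the article for baseline data), the row-mean-score test, or a proportional-odds model with arm as a three-level factor. The cost is wording, plus about 10 points of power if the effect is truly monotone in arm order. If a gradient is in fact the hypothesis, the alternative is to state the arm order and scores in advance with the reason, and accept the blindness to the middle arm.
- **Bands.** Make them disjoint, for example 75–89 good and 60–74 fair, before any data are classified. This costs nothing.
- **Motion domain.** Where it is scored postoperatively, derive it from the goniometer measurements taken at the blinded researcher's assessment. The visits and motion measurements are already planned, so this is a form and wording change.
- **Stability domain.** Leave it as it is on this evidence. Having the assessor supply it could require a procedure the article does not describe.
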